## Abstract

**Background:**

Being active in sports has many positive health effects. The direct effects of engaging in regular physical activity are particularly apparent in the prevention of several chronic diseases, including cardiovascular disease, diabetes, cancer, hypertension, obesity, depression, and osteoporosis. Besides the beneficial health effects of being active, sports participation is unfortunately also associated with a risk of injuries.

In the case of many sports injuries (eg, winter sports) preventive measures are not compulsory, which means that a behavioral change in sports participants is necessary to increase the use of effective measures, and subsequently prevent or reduce injuries in sports.

**Objective:**

The evidence-based Wintersportklaar online intervention has been developed to stimulate injury preventive behavior among skiers and snowboarders. In this article, the design of the effectiveness study will be described.

**Methods:**

A randomized controlled trial with a follow-up period of four months during the winter sport season will be conducted. The participants consist of inexperienced skiers and snowboarders. At baseline, skiers and snowboarders in the intervention and control groups are asked to report the injury preventive measures they usually take during their preparation for their winter sport holiday. One and three months after baseline, skiers and snowboarders are asked to report retrospectively in detail what measures they took regarding injury prevention during their current winter sport preparation and winter sport holiday. Descriptive analyses (mean, standard deviation, frequency, range) are conducted for the different baseline variables in both study groups. To evaluate the success of the randomization, baseline values are analyzed for differences between the intervention and control groups (chi square, independent *T* tests and/or Mann-Whitney test). Chi square tests and/or logistic regression analyses are used to analyze behavioral change according to the intention to treat principle (as initially assigned).

**Results:**

The project was funded in 2016 and enrolment was completed in 2017. Data analysis is currently under way and the first results are expected to be submitted for publication in 2018.

**Conclusions:**

To combat the negative side effects of sports participation, the use of injury preventive measures is desirable. As the use of injury prevention is usually not compulsory in skiing and snowboarding, a behavioral change is necessary to increase the use of effective injury preventive measures in winter sports.

**Trial Registration:**

Dutch Trial Registry NTR6233; http://www.trialregister.nl/trialreg/admin/rctview.asp?TC=6233 (Archived by WebCite at  http://www.webcitation.org/6wXZPzjUi)

## Introduction

Skiing and snowboarding are very popular winter sports worldwide, including among Dutch residents. Nearly one million Dutch snow sport fanatics travel each year to the mountains to spend their winter holidays in the snow, with Austria, France, Germany, Switzerland, and Italy being the most popular destinations [1]. Besides the beneficial health effects of being active, both skiing and snowboarding are also associated with a risk for musculoskeletal injuries and traumatic brain injury (42 injuries per 1,000,000 person-years for skiers and 19 injuries for snowboarders in America or 0.6 injuries per 1,000 skier days in Austria) [2-4]. Although the injury rate among skiers in Austria has decreased in recent years, attention to injury prevention should be encouraged due to the severity of these injuries [2,4].

Known risk factors for the occurrence of snow sport injuries are snow sport experience, rented equipment, weather conditions, speed, fatigue and technical errors [5,6]. The development of safer skiing environments and the use of injury preventive measures—especially a winter sport helmet—might prevent or reduce injury severity among skiers and snowboarders. However, because injury preventive measures such as helmet use for adults and wrist guard use for snowboarders in general are not compulsory on the ski slopes, a behavioral change in skiers and snowboarders is necessary to increase the use of those measures and subsequently prevent or reduce injuries in winter sports.

Accordingly, a scientific research project has started in the Netherlands (funded by ZonMW, the Netherlands Organization for Health Research and Development). The aims of this project are: (i) to develop an evidence-based intervention to stimulate injury preventive behavior among skiers and snowboarders; and (ii) to evaluate the effectiveness of the developed intervention. The effectiveness of the developed intervention will be evaluated through a randomized controlled trial. This article describes the design of this study.

## Methods

The Consolidated Standards of Reporting Trials (CONSORT) statement is followed to describe the design of the study [7]. This statement is a checklist intended to improve the quality of reports of randomized controlled trials.

### Objective and Hypothesis

The objective of the study is to evaluate the effectiveness of the Wintersportklaar intervention (www.wintersportklaar.nl; in Dutch) on injury preventive behavior among skiers and snowboarders. The hypothesis of this study is that the developed intervention would lead to a 10% increase in favorable injury preventive behavior in the intervention group in comparison to the control group.

### Study Design

A randomized controlled trial with a follow-up period of 4 months during the winter sport season will be conducted (see Figure 1). The study is registered in the Dutch Trial Registry (ID: NTR6233).

### Participants and Recruitment

The participants consist of inexperienced skiers and snowboarders. Inclusion criteria are: (i) less than five weeks of winter sport lessons or; (ii) less than two weeks of winter sport holiday per year or; (iii) less than five weeks of winter sport experience or; (iv) low physical fitness. An exclusion criterion is cross-country skiing.

Because of the relatively short duration of the winter sport season, participants can preregister 2 months before the start of the study. Participants are recruited via social media networks (ie, Facebook, websites, Twitter, LinkedIn) of the participating organizations (Dutch Consumer Safety Institute and Dutch Skiing Association). All the preregistered participants will receive the baseline questionnaire.

### Ethics, Consent and Permissions

The study protocol has been approved by the Medical Ethics Review Committee of the Academic Medical Center (W16-335 #16.417; Amsterdam, the Netherlands). Participants willing to take part in the study have to give their informed consent prior to the start of the baseline questionnaire. The flow of the participants is presented in Figure 1.

### Sample Size and Allocation

In this study, the assumption is made that a 10% increase in favorable injury preventive behavior in the intervention group compared with the control group can be achieved. To achieve 80% power with a significance level of 0.05, and taking into account a potential loss to follow-up among participants of 10% over the winter sport season, the sample size calculation reveals that 423 skiers and snowboarders per study group are needed in this study. Eligible participants will simultaneously be allocated at random to the intervention or control group after T0, using a computerized random number generator (the ASELECT function in Excel). No restrictions will be imposed for the allocation; simple randomization will be performed. All steps in the randomization process will be done by 1 researcher.

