### Intervention

The Wintersportklaar intervention has been developed according to the steps of Intervention Mapping (IM) and Knowledge Transfer Scheme [8-10]. The Fogg Behaviour Model (FBM) to achieve behavior change formed the basis for this development [11]. More information on the development of Wintersportklaar is available in [name], [name] & [name] (under review).

Wintersportklaar will be made available exclusively to the participants within the intervention group, and is an evidence-based intervention developed to stimulate injury preventive behavior among skiers and snowboarders. The development of the intervention was a collaboration between snow sport experts and the target group. According to the Dutch winter sport experts who were consulted, the skill level and the physical fitness level of skiers and snowboarders are the two main dimensions involved in the risk of winter sport injuries.

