### Injury Preventive Behavior

In our study, our main outcomes measure injury preventive behavior defined as: (i) taking winter sport lessons; (ii) performing strength exercises; (iii) the use of protective equipment; and (iv) knowledge of the 10 FIS rules for the conduct of safety in winter sport. Each injury preventive topic is divided into preparatory acts like searching for information about injury preventive measures, buying a winter sport helmet, etc, and structural injury preventive measures (eg, wearing a helmet, taking lessons). Taking winter sport lessons consists of two preparatory acts and three structural injury preventive measures. Performing strength exercises consists of two structural injury preventive measures, and the use of protective gear consists of three preparatory acts and three structural injury preventive measures. Finally, knowledge of the 10 FIS rules for the conduct of safety in winter sport consists of three preparatory acts. All injury preventive behaviors are assessed through single questions (eg, Did you buy a winter sport helmet after the start of this study? Yes/No/Not applicable).

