### Procedures

At baseline, respondents will be asked about their winter sport demographic characteristics, winter sport skill level, physical fitness, current injuries and physical complaints, winter sport preparation, and winter sport injury preventive measures. Furthermore, skiers and snowboarders in the intervention and control group will be asked to report the injury preventive measures they usually take during their preparation for their winter sport holiday. One month and three months after baseline, skiers and snowboarders will be asked to report retrospectively in detail what they had done up until then regarding injury prevention during their current winter sport preparation and holiday. In the follow-up measurements, respondents will be asked about any injuries they suffered during their winter sport preparation and holidays. In our study, an injury is defined as an event during skiing or snowboarding after which the participants have to stop their winter sport activities or are unable to participate in another winter sport activity [12-15]).

For all three measurements, an online form will be sent by email by 1 researcher through SurveyMonkey, an online questionnaire system (www.surveymonkey.nl). The first reminder will be sent after 1 week if no response is received. A second reminder will be sent after 2 weeks if no response is received.

The intervention group will be additionally questioned about their use and valuation of the Wintersportklaar intervention. The evaluation of its effectiveness will not take place in an experimental setting; participants in the intervention group will be given access to the intervention, but no further conditions are applied to the use of the intervention. In the questionnaires given at one month and three months, the intervention group will be asked about their use of the intervention, the appeal of the intervention, the behavioral actions they took after being exposed to the intervention, their intention to use the intervention again, and how they would want to be informed about the intervention. If participants indicate that they do not want to use the intervention, they will be asked to explain their decision in detail.

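### Questionnaire timing and recall start at baseline or earlier, while access starts only after a later joint allocation, so acts and holidays before access can count as outcomes and dilute the contrast

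*Protocol article*

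**What the plan says.** The Protocol article sets three clocks.

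- **Allocation and access.** Under Sample Size and Allocation: "Eligible participants will simultaneously be allocated at random to the intervention or control group after T0". Under Intervention: "Wintersportklaar will be made available exclusively to the participants within the intervention group". Nobody can use the site before allocation.
- **Questionnaires.** Under Procedures: "One month and three months after baseline, skiers and snowboarders will be asked to report retrospectively". The anchor is baseline, not allocation or access.
- **Recall.** The same sentence asks what was done "up until then regarding injury prevention during their current winter sport preparation and holiday". The one item shown, under Injury Preventive Behavior, starts elsewhere: "Did you buy a winter sport helmet after the start of this study". Neither starting point is allocation. Injury recall under Procedures also covers preparation and holidays, with no lower limit at allocation.

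Three further statements bear on this. Under Participants and Recruitment, "participants can preregister 2 months before the start of the study", and preregistered people then receive the baseline questionnaire. No entry criterion there requires a holiday still to come. For all three measurements a reminder goes out after one week, and "A second reminder will be sent after 2 weeks if no response is received".

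**The concern.** Allocation can influence only what happens after it. If the outcome window opens earlier, it takes in lessons booked, information looked up, gear bought, holidays taken and injuries suffered before anyone in the intervention arm could open the site. Those events occur equally often in both arms in expectation. They add no contrast and leave fewer participants or items in which a contrast can appear, so an intervention that works could look ineffective.

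The one-month comparison is the most exposed, because a pre-access gap of given length takes up a larger part of one month than of three. Power is planned at only 80%, so there is little to spare.

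**Working it through.** **1. The order of events.** Preregistration precedes the start of the study, and preregistered people then receive T0, so study start is not after T0. Allocation follows T0, and access follows allocation. The order is therefore preregistration, study start, T0, allocation, access.

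| Rule | Window opens at | Takes in time before access? |
|---|---|---|
| General recall (Procedures) | this season's preparation, no lower limit | yes, including acts before T0 |
| Helmet item (Injury Preventive Behavior) | start of the study | yes, from study start to allocation |
| Injury recall (Procedures) | preparation and holidays, no lower limit | yes |

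**2. Length of the gap.** It is not stated. A joint draw that waits for all T0 responses cannot precede the second reminder, at 14 days. If baseline means the T0 mailing and access starts 14 to 21 days later (both assumptions), a 30-day window leaves 30 − 14 = 16 down to 30 − 21 = 9 days after access. A 14-day gap would be 14/30 = 47% of one month but 14/90 = 16% of three months. If baseline means the close of T0, the gap could be near zero.

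**3. The planned sample size.** Inputs from Sample Size and Allocation: 10% increase, 80% power, significance level 0.05, 10% loss, 423 per group. The control rate is not given, so 423 does not follow from these inputs alone. Assuming 50% against 60%, two-sided, with unpooled variance:

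n = (1.960 + 0.842)² × (0.50×0.50 + 0.60×0.40) / 0.10² = 7.85 × 0.49 / 0.01 ≈ 385 per arm, and 384.6 × 1.1 ≈ 423.

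Other assumed rates and variance formulas come within 3% (for example 418 or 432), so this match does not establish the sponsor's control rate. After 10% loss, 423 × 0.9 ≈ 381 per arm can be analysed.

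**4. Illustrated dilution.** Let f be the share of participants whose outcome could not be affected. The documents do not give f. The observed difference is d = 0.10 × (1 − f), and

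power = Φ( d / √[(p₁(1−p₁) + p₂(1−p₂)) / 381] − 1.96 ), with p₂ = p₁ + d.

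For f = 0 and p₁ = 0.50: 0.10 / √(0.49/381) = 0.10 / 0.03586 = 2.789, and Φ(0.829) = 0.796.

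| f (assumed) | d | Power, controls 50% | Power, controls 30% |
|---|---|---|---|
| 0 | 0.10 | 0.796 | 0.829 |
| 10% | 0.09 | 0.707 | 0.747 |
| 20% | 0.08 | 0.604 | 0.648 |

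**The case against.** The article condenses a fuller protocol. It shows one questionnaire item and a summary of the rest, and the flowchart is not available. The word simultaneously might mean in parallel to both arms and not one joint draw. Baseline might mean the close of T0. Study Design gives a four-month follow-up while the last questionnaire comes at three months, which would fit a T0 phase of about a month, though this is not stated. T0 also asks about winter sport preparation, and Statistical Analysis speaks of behavioural change, so some acts already done may be on record.

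Much of this stands as a limit on size. It does not remove the point: even if each person were allocated on completing T0, recall over the current preparation would still reach back before access. Nor does the article say that acts already done are subtracted. Its baseline behaviour question is described as what people usually do.

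A reader might infer more than the text allows:

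- *That helmets bought during preregistration count.* The helmet item starts at study start, which excludes them. Only items using the current-preparation window reach back that far.
- *That anyone with an early act is beyond influence.* Someone who booked lessons early can still change gear use or learn the FIS rules after access. Zero effect is fully credible only for holidays finished before access, a smaller group of unknown size.
- *That the loss of power is a finding about this trial.* It is an illustration with an assumed f, and one f for all outcomes probably overstates it.
- *That one arm is favoured.* Pre-access events are equal in expectation between arms.

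**Conclusion.** The point holds as a mismatch between stated rules. Access begins at allocation, while the questionnaire clock begins at baseline and recall begins with the current preparation or study start. Events between study start or T0 and allocation can count as outcomes; so can earlier acts this season, for items using the current-preparation window. The consequence is dilution towards no effect, most at one month. The comparison between arms remains valid.

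The size cannot be determined from the article. If 10% to 20% of participants could not be affected, the planned 10 points become 9 to 8 and power drops from about 80% to about 71% to 60%. That rests on an assumed f, 381 per arm and 50% in controls. The reading of allocation as one joint draw affects only the waiting-time part.

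**What to change.** **Design.** Send both questionnaires one and three months after the common allocation date. Word every outcome and injury item, in both arms, to start at that date. Record at T0 the planned departure date and the acts already done this season.

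**Data already collected.** Results says that enrolment is complete and analysis under way, so mailing and wording may no longer be open to change. Keep the intention-to-treat analysis of all randomised participants as the main analysis. Adjust it for preparation recorded at T0. Add a sensitivity analysis that leaves out participants whose departure, by a date recorded before allocation, came before allocation. Allocation cannot have influenced such a date, so the remaining groups are comparable as randomised.

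If departure dates were collected only at follow-up, they exist only for responders, and response may differ by arm. Report that analysis as exploratory; it should not replace the main analysis. In either case, state the interval from T0 to allocation and interpret a null one-month result in that light.

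**Cost.** For the design change, small changes to wording and mailing dates and a few added T0 questions. For the analysis, slightly fewer participants in the sensitivity analysis. That analysis does not remove pre-access acts by people who travel later; the T0 adjustment can address these only as far as T0 recorded them.

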## Discussion

This article describes the design of a study that will evaluate the effectiveness of an intervention on injury preventive behavior in skiers and snowboarders. A major challenge of this study is related to the recruitment of participants and their adherence to this study. A total of 848 skiers and snowboarders will enroll for this study. To recruit respondents, several strategies are used (eg, social media such as Facebook, LinkedIn, and Twitter, and the possibility to preregister for the study). In a previous study, we also used social media to recruit skiers and snowboarders. Within two weeks, we received 300 responses, without the use of any rewards for participants or paid advertisements on social media. For this study, respondents will be offered a chance to win a money prize if they complete all three questionnaires. The chance to win a reward (€250) is used to enhance the willingness of skiers and snowboarders to participate in the study and the respondents’ adherence to the study, even after their winter sport holidays are over. In combination with the possibility to preregister for the study and the use of paid advertisements on (eg, Facebook), we believe that the recruitment of 848 skiers and snowboarders will be challenging, but feasible.

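### Unrestricted allocation of the whole list after T0 is valid, but one recorded, seeded draw stratified on baseline skill and fitness, with both adjusted for in the analysis, would be better at almost no cost

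*Protocol article*

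**What the plan says.** In Sample Size and Allocation, the protocol article allocates eligible participants simultaneously after T0, "using a computerized random number generator (the ASELECT function in Excel"). It continues: "No restrictions will be imposed for the allocation; simple randomization will be performed. All steps in the randomization process will be done by 1 researcher". The same section gives the target: "423 skiers and snowboarders per study group are needed in this study".

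Four other places bear on the point:

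- **Procedures:** skill level and physical fitness are among the items asked at baseline, so they are in hand before allocation. This section also says that "an online form will be sent by email by 1 researcher through SurveyMonkey", without saying whether this is the researcher who randomizes.
- **Intervention:** the consulted experts regard skill and fitness as the two chief dimensions of injury risk, and the advice is tailored to them.
- **Statistical Analysis:** baseline differences between the groups are tested to judge the randomization. Chi-square tests and/or logistic regression are used for the outcome, and no adjustment covariates are named.
- **Results:** enrolment was completed in 2017 and analysis is under way.

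**The concern.** Two features of the allocation give away something that could be had for nothing.

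First, one person carries out every step in a spreadsheet, at a time when baseline answers are available. The article describes no seed, locked list or stored result by which someone else could confirm which draw was used. Participants know whether they have access to the intervention, and they report their own behaviour. In such a trial, a verifiable allocation is one of the few safeguards left.

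Second, the usual reason for caution about restricted randomization is that staff might predict the next assignment. That does not apply when the whole list is allocated at once. Stratification on skill and fitness would therefore add no predictability. Leaving it out accepts chance imbalance on characteristics that plausibly relate to lessons, exercises and use of protective gear.

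**Working it through.** **Inputs from Sample Size and Allocation.** The effect is given as "the assumption is made that a 10% increase in favorable injury preventive behavior in the intervention group compared with the control group can be achieved", the error rates as "To achieve 80% power with a significance level of 0.05", and attrition as "taking into account a potential loss to follow-up among participants of 10% over the winter sport season". The article does not state the control proportion, the sidedness of the test or the allocation ratio. I assume 50% against 60%, a two-sided test and 1:1 allocation.

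**Step 1: reproduce 423.** Unpooled formula for two proportions, per group:

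n = [p1(1−p1) + p2(1−p2)] × (1.960 + 0.842)² / (p2−p1)² = (0.25 + 0.24) × 7.849 / 0.01 = 384.6.

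Multiplied by 1.1 this is 423.05, which matches the stated figure. Dividing by 0.9 instead gives 427.3. An assumption of 40% against 50% gives the same result. So 423 is the output of a sample-size formula, that is, a target.

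**Step 2: group sizes under simple randomization.** With N = 2 × 423 = 846, the size of one group is Binomial(846, 0.5).

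- Standard deviation: √846 / 2 = 14.5.
- Central 95% range: 395 to 451.
- Probability of exactly 423/423: 2.7%.
- The Discussion gives another total ("A total of 848 skiers and snowboarders will enroll for this study"). With 848, the probability that both groups reach 423 is 8.2%.

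**Step 3: what unequal groups cost.** At the 95% limit of 395/451, the efficiency relative to an equal split is 4 × 395 × 451 / 846² = 0.996. Power after 10% loss:

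| Split of 846 | 50% v 60% | 20% v 30% |
|---|---|---|
| 423/423 | 79.3% | 89.1% |
| 395/451 | 79.2% | 89.0% |
| 375/471 (about 1 in 1000) | 78.8% | 88.7% |

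At the 95% limit the loss is 0.15 points in the first scenario and 0.19 in the second. Group size is therefore not a reason to change the method.

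**Step 4: chance imbalance on a baseline characteristic.** The article gives no prevalence for low skill or low fitness. I assume 50%, which gives the largest spread.

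SD of the difference = √[0.5 × 0.5 × (1/423 + 1/423)] = √0.001182 = 0.034, or 3.4 percentage points. The 95% range is ±1.96 × 3.44 = ±6.7 points.

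**Step 5: effect on an unadjusted estimate.** Assume, for illustration only, that the characteristic shifts the proportion with favourable behaviour by 20 points. An imbalance of 6.7 points then moves the unadjusted difference by 0.067 × 20 = 1.3 points, against a target of 10. Stratification or adjustment would largely remove this. At a more typical imbalance of one standard deviation, the shift is 0.034 × 20 = 0.7 points.

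**The case against.** The strongest reply is that nothing here is wrong. Simple randomization is valid at about 423 per group. Chance imbalance is not bias, and the significance level already allows for it. Consent precedes the baseline questionnaire (Ethics, Consent and Permissions), and everyone is allocated at once, so nobody could be enrolled or turned away on the strength of a known or predicted assignment. A condensed article may also leave seed, storage and audit trail to the full protocol. All of this stands, and it is why the point is an improvement and not a flaw.

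A reader might infer two stronger things:

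- **That the draw was, or would be, repeated until the groups looked balanced.** The order of events invites the thought: baseline data in hand, one researcher, and a planned test of whether randomization succeeded. But the article says nothing about redrawing, nor about whether the values were frozen. The text leaves the possibility open and does not support the inference.
- **That the design fails to deliver 423 per group.** An exact 423/423 split is indeed unlikely, but the article calls 423 the number needed and does not promise it as a realised group size. Steps 2 and 3 show that the shortfall has no material effect.

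Two practical objections also hold. The four-cell fitness and skill class is produced by the questionnaire inside the intervention, which controls do not see, so strata would have to be built from the T0 items. And the article does not list skiing versus snowboarding explicitly among those items, so discipline can be used only if T0 records it. Further, because participants are selected for inexperience or low fitness, too many strata would leave some sparse.

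**Conclusion.** The point holds as a minor, free improvement. The allocation is valid, but as described it does not provide one reproducible draw, and it forgoes balance on two recorded characteristics that the article itself treats as important.

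The size is modest: an SD of about 3.4 points for the imbalance on a single 50%-prevalence characteristic, and about 1.3 points of displacement in an unadjusted estimate at the 95% limit. These figures rest on the assumed prevalence, the assumed 20-point association and an equal split of 846. The article links skill and fitness to injury risk. Their link to the behavioural outcomes is plausible but not documented.

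**What to change.** **If allocation is still to be done:**

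1. Close T0, settle eligibility and lock the list of study identifiers.
2. Run one prespecified script, once, with a seed recorded beforehand.
3. Allocate 1:1 by random permutation within a few strata, such as low or sufficient skill by low or sufficient fitness, defined from the T0 items (and discipline if T0 records it). Strata of odd size may leave the groups a few participants apart, which does not matter.
4. Archive the script, seed, list and result.

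**If allocation has already been done,** as completed enrolment suggests, report who made the draw, whether it was made once, when the eligible list was locked, and how the result was fixed and stored.

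**In either case,** adjust the logistic regression in Statistical Analysis for baseline skill and fitness (and discipline if recorded). Do this whatever the baseline tests show, and specify it before the group comparison is seen. If that comparison has already been run, say so. An adjusted odds ratio is conditional on the covariates, so also give an adjusted difference in proportions, which can be set against the 10% target.

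The cost is a few lines of script or a short paragraph of reporting, plus the covariate terms. No further participants, staff or data are needed.
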